### Scale-up implementation evaluation

Running alongside the cluster RCT will be a scale-up implementation study. This evaluation will be a multiple cohort design, with all schools receiving the intervention. Measurement will be guided by the RE-AIM framework [73] and will occur at baseline, 12 and 24 months for each cohort.

#### Participants and procedures

Participants will include principals, teachers and students at government-funded primary schools in NSW. There will be no exclusion criteria for principals or teachers within these schools. To be included in the study at least 50 % of Stage 2 (Years 3 and 4) teachers must be willing to participate in the program, at least one staff member must be willing to be an *iPLAY* leader, and the principal must provide consent for the program to run in the school. All students who are enrolled in Years 3 or 4 (Stage 2) at baseline and who are able to participate in physical activity will be eligible for the study, except for students enrolled in ‘Schools for Specific Purposes’ (i.e., for students who require intensive levels of support). In these schools, teachers will be eligible to participate in the study, but students will not be asked to complete outcome assessments.

Principals and teachers will provide written informed consent to participate in the scale-up implementation study. Passive consent procedures will be used regarding student participation; newsletters will be sent home and will ask parents to indicate if they do not wish their child to participate in the study.

#### Measures

##### Reach

We will examine the extent to which participating schools are representative of the NSW population, in terms of school size, SES, and location. Once a school is recruited into the study we will employ a questionnaire to ask the principal to identify the “single most important reason for your decision to participate”. At the end of recruitment, we will purposively sample 100 schools (according to size, SES, and location) that do not volunteer and follow-up by telephone to determine reasons for non-participation.

##### Effectiveness

We will conduct a reduced examination of effectiveness in the scale-up implementation study compared with the cluster RCT. Assessments will include all questionnaires and standaridized tests of numeracy and literacy from the cluster RCT. Other measures (e.g., 20 m multistage fitness test, accelerometers, fundamental movement skills, and cognitive control) will not be obtained in the scale-up implementation study.

Principals and teachers will complete online questionnaires. Classroom teachers will also administer an online questionnaire to their students to complete self-report measures. Questionnaires will be administered to principals, teachers, and students at baseline, post-intervention (12 months) and maintenance (24 months).

##### Adoption

We will examine the proportion of schools from the NSW population that volunteer and participate in the program. We will assess teacher level adoption by examining the proportion of teachers who complete each aspect of the training, including attendance at face-to-face workshops and completion of online components, as well as participation in mentor meetings, peer observations and small group discussions.

##### Implementation

We will monitor implementation as per Table 1 (curricular and non-curricular components).

##### Maintenance

Using the procedure described above, we will re-examine effectiveness and implementation 24 months after baseline. To further understand barriers and facilitators to implementation, we will conduct semi-structured interviews with purposively selected principals (*n* = 15), teachers (*n* = 15) and students (*n* = 15). Sampling will ensure that interview participants are drawn from schools in which the intervention had strong effects, weak effects and no effects. Thematic analysis of transcripts will indicate ways to improve implementation prior to further dissemination.

#### Statistical analyses

The scale-up implementation study will be assessed with a focus on descriptive statistics concerning reach, adoption, implementation, and maintenance. We will also use linear regression to explore the impact of school and community characteristics on program reach. We will use linear mixed model analysis to examine changes in outcome variables from baseline to 12-months and 24-months (i.e., effectiveness). These effects will be estimated for the entire sample as well as in key sub-populations (e.g., across teacher sex, school average SES, teachers with high vs low internet self-efficacy). Where possible, we will compare *iPLAY* schools with expected values within the population (e.g., NAPLAN scores in similar schools, physical activity participation) from other data sources such as NSW School Physical Activity and Nutrition Survey [66]. We will also compare outcomes at 12 months (post-intervention) for Cohort 1 with baseline levels for Cohort 2, taking advantage of the natural experiment that is inherent in the design of the study.

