**Fig. 1 Fig1:**
[figure not shown]
Modified CONSORT Flow Diagram

All teachers in each school selected for the cluster RCT and scale-up implementation study will be invited to complete the *iPLAY* intervention (or attention control intervention for 10 schools in the cluster RCT). However, only the student cohorts in Years 3 and 4 at baseline will complete outcome assessments (i.e., students in Years 3 and 4 at baseline, students in Years 4 and 5 at post-intervention [12 months], students in Years 5 and 6 at maintenance [24 months]). These students will be available for assessment at all time-points (c.f. most Year 5 and 6 students will leave the school by 24 months), and will have the cognitive ability to complete the questionnaires (c.f., Years 1 and 2). In addition, these years represent the ideal period to develop fundamental movement skill competency [30], which may help prevent the decline in physical activity typically observed during the transition from childhood to adolescence [31].

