#### Economic evaluation

The research question for economic evaluation of the scale-up implementation study will be to assess, from a societal perspective, the cost-outcome of scaling up the *iPLAY* project (rollout and implementation to 160 schools) in primary schools within NSW to assess intervention affordability and sustainability.

The economic analysis will be a cost-outcome description as the one-arm design of the scale-up implementation study does not include a control arm (which is necessary for determination of comparative cost-effectiveness). The primary economic analysis will comprise three components: a cost analysis; an outcome analysis and the relationship between cost and outcomes for the intervention. Costing of the intervention using opportunity cost principles will involve the following steps:Identification of costs to be included, using ‘pathway analysis’, where activities in all stages of the roll out of the *iPLAY* project are fully specified; A societal perspective and steady state operation of the intervention will be assumed (up and running to its full effectiveness potential). Costs will largely relate to the time costs of specialist mentors, leaders, classroom teachers, and school principals (using opportunity cost principles). Any administrative resources used at the program management level also will be identified and included, although research-driven activities will be separated from the activities that would be carried out should the program be adopted by primary schools;Measurement of the resources consumed in natural units (number of hours spent by specialist mentors/leaders within school/principals to deliver the intervention, number and length of school visits, etc.);Valuation of these resources in monetary units (using 2018 as the reference year).

In addition, variations in delivery costs of the *iPLAY* intervention between participating schools will be identified in order to determine any factors that may impact on the roll out of this program throughout NSW primary schools and its adoption in other jurisdictions.

The economic outcomes for the scale-up implementation study will be presented as total costs, average costs per child and per school, separately from the intervention and maintenance periods. The relationship between costs and outcomes will be reported as average cost per outcome.

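### The scale-up study labels pre-post change as effectiveness although its pupils age one to two school years, and neither planned comparator, as worded, separates ageing from the programme

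*Protocol article*

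**What the plan says.** The scale-up evaluation is described thus: "This evaluation will be a multiple cohort design, with all schools receiving the intervention". Its Statistical analyses section says: "We will use linear mixed model analysis to examine changes in outcome variables from baseline to 12-months and 24-months (i.e., effectiveness". It goes on to call these changes effects, to be estimated overall and in sub-populations.

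The Design section fixes who is measured: pupils in Years 3 and 4 at baseline, then "students in Years 4 and 5 at post-intervention [12 months], students in Years 5 and 6 at maintenance [24 months".

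On content and timing, the Effectiveness section says: "Assessments will include all questionnaires and standaridized tests of numeracy and literacy from the cluster RCT". It adds: "Questionnaires will be administered to principals, teachers, and students at baseline, post-intervention (12 months) and maintenance (24 months". Fitness, accelerometry, movement skills and cognitive control are not measured in the scale-up study.

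The Statistical analyses section names two comparators. One is expected population values, used where they can be had, with NAPLAN in similar schools and activity participation as examples. The other is Cohort 1 at 12 months against Cohort 2 at baseline. The RCT control schools are not mentioned.

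The scale-up Economic evaluation section acknowledges that "the one-arm design of the scale-up implementation study does not include a control arm (which is necessary for determination of comparative cost-effectiveness", and for that reason restricts itself to a cost-outcome description.

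**The concern.** Self-reported activity, enjoyment, effort and well-being may all shift between Year 3 and Year 6 without any programme. The Design section itself refers to a typical fall in physical activity as children approach adolescence. A mixed model for change from baseline in treated schools estimates programme effect plus age trend and cannot divide the two. The bias can go either way: a falling outcome could hide a benefit, and a rising one could mimic it.

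The article treats the missing control arm differently in two places. It limits what the economic analysis may claim but places no such limit on the effectiveness analysis of the same schools. With 160 schools, sampling error is likely to be small, so a modest age trend could be reported as an effect of iPLAY at scale.

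**Working it through.** **1. The plan's own figure.** The only power figure is for the RCT: effect .35, ICC .09 (class) and .01 (school), 1080 pupils, 60 classes, 20 schools, power .91. That is 18 pupils per class and 54 per school.
- Variance of a school mean, in SD² units: .01 + .09/3 + .90/54 = .0567.
- SE of the arm difference: √(4/20 × .0567) = .1065.
- Power at two-sided 5% (alpha assumed): Φ(.35/.1065 − 1.96) = .908, against .91 stated.

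The figure reproduces. The point does not depend on it, but it supplies the variance used below. No precision figure is given for the scale-up analysis.

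**2. Age shift in each comparison**

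| Comparison | School years compared | Gap |
|---|---|---|
| Scale-up, baseline to 12 months | 3-4 to 4-5 | one year |
| Scale-up, baseline to 24 months | 3-4 to 5-6 | two years |
| Cohort 1 at 12 months v Cohort 2 at baseline | 4-5 v 3-4 | one year |
| Cohort comparison at 24 months | not planned | – |

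Only Year 4 occurs on both sides of the cohort comparison. Year 5 appears only in Cohort 1 and Year 3 only in Cohort 2.

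**3. How small a trend would register.** Assumptions, none from the documents: the fitness ICCs apply to questionnaire outcomes; there are 54 pupils per school; the baseline to follow-up correlation r is .3 to .7 at every level.
- SE of mean change in 160 schools = √(.0567 × 2(1−r)/160).
- Smallest significant observed change = 1.96 × SE.
- Chance of a significant result with no programme effect and drift δ = Φ(δ/SE − 1.96) + Φ(−δ/SE − 1.96).

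| r | SE (SD) | 1.96 × SE | δ = .02 | δ = .05 | δ = .10 |
|---|---|---|---|---|---|
| .3 | .022 | .044 | 15% | 61% | 99% |
| .5 | .019 | .037 | 19% | 76% | ~100% |
| .7 | .015 | .029 | 28% | 93% | ~100% |

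**4. Precision of a comparison with the 10 RCT control schools.** Same assumptions.
- SE of the difference in change = √(.0567 × 2(1−r) × (1/160 + 1/10)).
- r = .3: .092 SD. r = .5: .078 SD. r = .7: .060 SD.
- Detectable with 80% power, normal multiplier 2.8: .26, .22 and .17 SD.
- With only 10 control schools, a t multiplier on 9 df (2.26 + .88 ≈ 3.14) is more cautious: .29, .24 and .19 SD.

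This contrast removes drift common to both groups, at about four times the SE of the uncontrolled change (√(.10625/.00625) = 4.1).

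**The case against.** Several arguments on the other side have force.

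- **The scale-up analysis is not wholly without comparators.** Two are named. Population values matched on school year could deal with ageing for NAPLAN or activity. The cohort comparison can be matched on Year 4, and an analysis plan may do so. This stands, but the first is conditional, with no source named for most questionnaire scales, and the second carries the age gap as worded and stops at 12 months.
- **The design already limits the claim.** Effectiveness is a RE-AIM heading, the article calls this a reduced examination, and the RCT gives the controlled estimate. No significance rule or success criterion is set for the scale-up study, so a reader cannot infer that every trend will be declared an effect. This lowers the weight of the point without removing it.
- **The RCT controls are not a clean comparator.** RCT schools are the closest matched pairs within strata. Their parents give written consent, whereas scale-up consent is passive. Research assistants collect RCT pupil data, whereas classroom teachers run the scale-up questionnaire. Scale-up groups start in four different terms, so most start in a different term from the RCT schools. Control teachers are offered My Science, which may move teacher confidence and engagement outcomes. All of this stands. A reader might infer that the RCT controls should replace the planned estimate; the documents do not support that.
- **The test scores are not shared at every wave.** NAPLAN is obtained in Years 3 and 5 only, so no pupil has scores at baseline, 12 and 24 months.
- **Teacher and principal outcomes are outside the ageing argument.** That is correct.

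A reader might also infer that choosing interviewees from "schools in which the intervention had strong effects, weak effects and no effects" is invalid. An age trend common to all schools leaves their ranking unchanged, so that purposive sampling needs no change on this ground.

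**Conclusion.** The concern holds for pupil outcomes in the scale-up study. The article equates one-arm change with effectiveness while the pupils grow one to two school years older, and neither planned comparator, as worded, isolates the programme. The age shift follows directly from the text. The numbers are illustrative: they rest on fitness ICCs applied to questionnaires, 54 pupils per school and a correlation of .3 to .7. On that footing an observed change of about .03-.04 SD is significant, and a pure drift of .05 SD would be declared significant in 61-93% of studies. The documents give no drift size, so how far the results would be biased, and in which direction, is unknown.

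The weight is moderate. The RCT, its primary outcome and its inference are untouched. The remedy is mainly wording plus one supplementary analysis.

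**What to change.** 1. In the scale-up Statistical analyses section, call the pre-post result change over time and drop the equation with effectiveness. State that ageing is not separated from the programme for pupil outcomes.
2. Match the Cohort 1/Cohort 2 comparison on school year, Year 4 with Year 4. Adjustment for Year in the full sample would lean on a model, since only Year 4 overlaps. The cost is that only Cohort 1 pupils who began in Year 3 and Cohort 2 pupils in Year 4 at baseline contribute, and 24 months remains uncovered.
3. Add, as a supplementary non-randomised analysis, the difference in change at 12 and 24 months between scale-up schools and the 10 concurrent RCT control schools on the shared pupil questionnaires. Adjust for baseline, ICSEA, location, school size, Year level, cohort and start term. Limit any NAPLAN comparison to Year 3 to Year 5 change.
4. Declare the limits with the result: wider intervals (SE about .06-.09 SD on the assumptions above, with only 10 control schools), different consent and data collection, matched-pair selection of RCT schools, and the offer of My Science to control teachers.

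No new data collection is needed; the cost is analysis wording and one further model.

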From within each cohort, we will select 10 schools to participate in the cluster RCT; the other 80 schools will participate in the scale-up implementation study. Selecting schools for the cluster RCT will involve a four-step approach. The aims of this process are to ensure that schools in the cluster RCT are: (i) broadly representative of schools in NSW and (ii) assigned to trial arms such that most school-level covariates (e.g., socioeconomic status [SES], geographic location) are balanced, thereby increasing the likelihood that children in the two conditions are similar on the outcome variables at baseline. The four steps are:*Stratification:* All schools that express interest in the study and are among the 90 selected to participate in each cohort will be stratified according to SES and geographic location. Given the number of schools is small, the stratification process will require relatively coarse groupings. The Index of Community Socio-educational Advantage (ICSEA) will serve as the SES variable. This index includes information regarding parental SES and Indigenous representation [33]. The index has a median of 1000 and ranges Australia-wide from 300 to 1300 indicating heavy negative skew [33]. NSW has a similar distribution ranging from 582 to 1202 with a median of 1003. We will split the sample into a higher SES stratum (ICSEA < =1003) and a lower SES stratum >1003. These strata will be further split by geographic distribution using the Australian Bureau of Statistics remoteness index by postcode. The index has 12 categories but this will be reduced to two: urban (less remote) and provincial (more remote). This process will produce four strata: (i) urban-higher SES, (ii) urban-lower SES, (iii) provincial-higher SES, and (iv) provincial-lower SES.*Match-pairing:* We will employ a Euclidian distance minimization strategy to create pairs of similar schools from within strata. The variables used in this minimization process will be: (i) ICSEA, (ii) school size (number of students enrolled), (iii) average scores on national standardized test of numeracy and literacy that are completed by all NSW children (see outcomes section for further details) and (iv) school participation (or not) in a state-wide physical activity and nutrition program, known as Live Life Well at School [34], that took place from 2008 to 2015.*Pair selection:* Once schools have been matched using the minimization procedure, we will select the two or three most similar pairs of schools from within each stratum to participate in the cluster RCT. Through this process, four schools will be selected from each of the provincial strata and six schools are chosen from each of the urban strata. This strategy will allow for calculation of average treatment effects and differences in treatment effects by strata.*Randomization*: Following baseline data collection, schools will be randomly assigned from within each pair to the experimental or control arm of the cluster RCT. An experienced statistician who is not part of the research team will conduct the randomization procedure using a computer-generated algorithm.

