#### Internet self-efficacy

An eight-item Internet self-efficacy scale will be used to assess teachers’ beliefs in their ability to utilize internet tools [68].

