##### Statistical analyses and sample size

We will test for between-arm differences in changes in student outcomes using linear mixed models with standard errors corrected for clustering. We will analyze data according to intention to treat principles (main analyses) and per-protocol principles (sensitivity analyses). We conducted a power analysis using procedures appropriate for complex nested designs [71]. In this analysis the effect size for between-arm differences in cardiorespiratory fitness (primary outcome) was conservatively set to .35 (note: effect in our efficacy trial was .54) with intraclass correlations based on our efficacy trial [21] (class = .09, school = .01). Analysis indicated that 1080 students from 60 classes in 20 schools (i.e., 3 classes per school) would provide power of .91.

We will explore potential moderators of intervention effects including children’s age, sex, ethnicity, weight status and SES, as well as baseline levels of cardio-respiratory fitness, physical activity and fundamental movement skill competence. As with the main analyses, we will employ a mixed modeling approach to explore moderation hypotheses by including appropriate interaction terms in the regression models. The trial is not powered to detect interactions; thus, we will employ a significance level of *p* < 0.1 to explore potential moderators. We will explore significant interaction terms by testing sub-groups differences on the primary outcome and selected secondary outcomes. We will also explore potential moderating effects of principal and teacher characteristics (e.g., specialist PE accreditation) on student outcomes.

Per protocol analyses will investigate the influence of *iPLAY* leaders’ and other teachers’ adoption and implementation of the intervention on student outcomes. Adoption will focus on the proportion of intervention training components completed (e.g., workshops attended and online tasks completed), while implementation will evaluate leaders’ and teachers’ utilization of strategies in their schools (as per Table 1).

Linear mixed models will be also used to examine potential mediating processes. For example, in our efficacy study we found that changes in fundamental movement skills mediated the effect of the intervention on children’s physical activity and cardiorespiratory fitness. Mediating effects will be estimated using a cluster-bootstrapped based product-of-coefficients test that is appropriate for cluster RCTs.

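### The scale-up analysis compares teachers with high and low internet self-efficacy, although the measure is an eight-item score; a continuous score-by-time interaction would use more of the information (minor, cheap to change)

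*Protocol article*

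**What the plan says.** Under *Scale-up implementation evaluation, Statistical analyses*, the effectiveness model is set out as follows: "We will use linear mixed model analysis to examine changes in outcome variables from baseline to 12-months and 24-months (i.e., effectiveness"). The article then names subgroups in which these changes will be estimated: "These effects will be estimated for the entire sample as well as in key sub-populations (e.g., across teacher sex, school average SES, teachers with high" versus low internet self-efficacy). The high/low wording is attached to internet self-efficacy alone. No cut point is given.

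The variable is described under *Teacher level measures, Internet self-efficacy*: "An eight-item Internet self-efficacy scale will be used to assess teachers’ beliefs in their ability to utilize internet tools". It is therefore a multi-level score and not a natural category like teacher sex.

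For moderators in the cluster RCT, *Statistical analyses and sample size* takes a different route: "we will employ a mixed modeling approach to explore moderation hypotheses by including appropriate interaction terms in the regression models".

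**The concern.** A high/low comparison treats all teachers on one side of the cut as alike, and treats two teachers just either side of it as different. If change in the outcomes rises or falls steadily with the score, the two-group contrast estimates that gradient less precisely than the score itself would.

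The question matters for this programme. The *Discussion* gives the project's purpose as finding out whether an efficacious intervention can be scaled up through online learning alongside face-to-face support. Whether results differ for teachers less confident with internet tools is an obvious roll-out question, and the scale-up study has many more schools than the RCT (160 against 20) in which to look at it. A less precise analysis makes a real gradient easier to miss.

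**Working it through.** **Is there a figure in the plan to reproduce?** Not for this analysis: no power, precision, cut point or score distribution is stated for the scale-up subgroups. The article's only power figure is 0.91 for fitness in the RCT. It reproduces at 0.908: the variance of a school mean is 0.01 + 0.09/3 + 0.90/54 = 0.0567, the standard error of the difference is √(2 × 0.0567/10) = 0.1065, and Φ(0.35/0.1065 − 1.96) = Φ(1.33), with two-sided 5% assumed. It has no bearing on the present point.

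**Inputs.** From the article: an eight-item score, grouped high against low, and a linear mixed model of change. Assumed here: a linear relation between score and change, a cut at the median, a two-sided 5% test, and a uniform or normal score.

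**Step 1: information kept.** For a linear gradient, the share kept by a two-group comparison is R² = [corr(X, indicator that X exceeds the cut)]². With a proportion p below the cut:

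- Uniform score: R² = 3p(1 − p). At p = 0.5 this is 0.75, a loss of 25%.
- Normal score: R² = φ(z_p)²/[p(1 − p)]. At p = 0.5 this is 0.3989²/0.25 = 0.637, a loss of 36%. The split needs 1/0.637 = 1.57 times the sample for the same precision.

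**Step 2: power.** Power after the split = Φ(√R² × (1.96 + z_power) − 1.96), ignoring the negligible opposite tail. From 80% power (z = 0.842, sum 2.802):

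- Uniform: 0.866 × 2.802 − 1.96 = 0.466, and Φ = 0.68.
- Normal: 0.798 × 2.802 − 1.96 = 0.276, and Φ = 0.61.

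**Step 3: dependence on the assumed starting power.**

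| Power with the continuous score | Uniform, median cut | Normal, median cut |
|---|---|---|
| 80% | 68% | 61% |
| 90% | 80% | 73% |
| 99% | 96% | 93% |
| 99.9% | 99% | 98% |

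**Step 4: dependence on the cut and the shape.** A 25/75 cut loses more: 1 − 3 × 0.1875 = 44% for a uniform score, and 1 − 0.3178²/0.1875 = 46% for a normal one. Among other simulated shapes cut at the median, a score piled up at both ends loses 22%, and negatively skewed bounded scores lose about 35% to 38%. These values show how far the result moves with the assumptions; none is an estimate for the actual scale.

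R² does not depend on the number of teachers. That is useful, because the article does not give the number, and a teacher-level score cannot be assessed by counting the 160 schools.

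**The case against.** The strongest reply is that this is an illustrative example in a mainly descriptive study. The article says so: "The scale-up implementation study will be assessed with a focus on descriptive statistics concerning reach, adoption, implementation, and maintenance". It claims no power for these comparisons, and high/low figures are easy for roll-out readers to use. Cut points and the exact form of the model are commonly left to a full analysis plan. All of this stands, and it keeps the point minor. It does not remove it, because the high/low grouping of a graded score is written into the text.

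Some stronger readings are tempting, and the article does not support them.

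- **School SES is also split in two.** The text lists school average SES as a subgroup variable without high/low wording, a number of groups or a cut. The split it does give, "We will split the sample into a higher SES stratum (ICSEA < =1003) and a lower SES stratum >1003", serves stratification and selection of RCT schools. If SES were reported in three or four groups and were normally distributed, the loss would be 21% or 14%.
- **The scale-up analysis has no test of the difference between groups.** The article is silent on this. Subgroup estimates can come from one mixed model with interaction terms, and nothing says that separate models will be fitted.
- **A large power loss is certain.** The fall depends on a starting power that the article does not give. From 99% it is only to about 96% or 93%.
- **The split damages the evidence on who the programme works for.** In a study where every school receives the programme, change by subgroup cannot establish that, however the score is coded. The controlled moderator analysis is in the RCT, which also plans to explore principal and teacher characteristics, though it does not name internet self-efficacy.

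**Conclusion.** The point holds for internet self-efficacy only. The article groups an eight-item score into high and low. For estimating a gradient this is less efficient than the score itself, and less efficient than the interaction approach the investigators already use for RCT moderators.

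Assuming a linear relation and a median cut, the loss is about 25% of the information for a uniform score and 36% for a normal one. A slope test with 80% power would fall to about 68% or 61%. The power loss shrinks when starting power is very high, and the information loss varies with the cut and the score's shape, neither of which is stated.

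Whole-sample effectiveness estimates are untouched. What is gained is a more precise description of how change varies with self-efficacy. This is a cheap improvement of minor importance and does not threaten the study's conclusions.

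**What to change.** In *Scale-up implementation evaluation, Statistical analyses*, enter the internet self-efficacy score as a continuous variable with a score-by-time interaction in the linear mixed model already planned. Add a quadratic or spline term as a check on linearity. Report the model-estimated 12- and 24-month change at stated low and high score values (for example the 10th and 90th percentiles), so the high and low display is kept. Teacher sex stays a category. Where school SES is examined, the school's ICSEA value can be entered as continuous in the same way; this is a suggestion and not a correction of a stated split.

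The cost is about one sentence of analysis wording, with no new data. The downside is the linearity assumption, which the quadratic or spline check covers.
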